**Exclusion Criteria:**

- > 65 years old
- presence of acute infectious disease
- antibiotic therapy (ongoing or in the previous <= 7 days)
- previous PPV23 or PCV7 vaccination
- Pregnancy
- Current immunomodulatory therapy
- Immunosuppression not HIV related

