**STUDY DESIGN**

This is a phase III, prospective, multicenter, pilot controlled study enrolling HIV-infected outpatients, aged 18–65 years with CD4 counts ≥200 cells/µL, pneumococcal vaccine-naïve.

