The purpose of this study is to evaluate serological response and prevalence of nasopharyngeal colonization by *S. pneumoniae* in HIV-positive non-hospitalized adults, following vaccination with one dose of PPV23, and in unvaccinated HIV-negative subjects.

To completion of the study “Serological Response to Antipneumococcal Vaccination and Impact on *Streptococcus Pneumoniae* Nasal Carriage in HIV Adults” (protocol code PCV13-HIV2011 EudraCT number 2011-004518-40) the present study will be conducted simultaneously, for a microbiological and serological monitoring in HIV-positive adults with previous PPV23 vaccination and in HIV-negative subjects, regardless their vaccination status. Correlation analyses between clinical-anamestic data, immune response and microbiological results and the comparison between the populations from the main study (EudraCT number 2011-004518-40 ; protocol code PCV13-HIV2011) and from this sub-study (protocol code PNEUMO-HIV 2011) will provide essential clinical and epidemiologic findings useful to choice the optimal therapy and prophylaxis to prevent the pneumococcal diseases in HIV-positive adults.

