**STUDY DESIGN**

This is a prospective, multicenter, pilot controlled study enrolling HIV-infected outpatients, aged 18–65 years with CD4 counts ≥200 cells/µL, previously vaccinated , and unvaccinated HIV-negative subjects as a control,

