**Inclusion Criteria:**

- > 18 years old
- obtained informed consent
- outpatient
- HIV with previous PPV23 vaccinatio (≤5years)
- HIV with CD4 ≥200 cells/µl in the last two evaluations before T0
- HIV negative regardless vaccination status

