**Sample size and study group selection**

Applying these criteria, 50 HIV-infected adult outpatients and 100 subjects HIV negative will be prospectively enrolled at two Infectious Diseases Clinical Centers in Central Italy (University Division of Infectious Diseases in Siena and Institute of Clinical Infectious Diseases, Catholic University of the Sacred Heart in Rome). All subjects will be required to sign a written informed consent before enrolling in the study.

At baseline, demographic, clinical and laboratory characteristics will be collected by patients interview.

At baseline, the enrolled HIV-positive patients will received one dose of the 23-valent vaccine (PPV 23); follow-up visits will be scheduled at 8 (time of second PCV13 dose), 24 and 48 weeks.

At baseline and at each visit clinical and anamnestic data from patients will be recorded; peripheral venous blood samples will be collected to assess humoral immune response against PPV23 serotype; nasopharyngeal swabs will be collected, in order to investigate the *S. pneumonia* presence. CD4+ T cell count and plasma HIV-RNA will be also monitored.

After each vaccine administration, short- (30 minutes), medium- (≤5 days) and long-term adverse reactions will be monitored.

Oppositely, HIV negative subjects will not receive any vaccination; only at baseline clinical and anamnestic data will be recorded; peripheral venous blood samples will be collected to assess humoral immune response against PPV23 serotype; nasopharyngeal swabs will be collected, in order to investigate the *S. pneumonia* presence.

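### In the sub-study, the inclusion list requires recent PPV23 in HIV-positive subjects and the exclusion list bars it, so the group the plan describes cannot enter as written

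*Supplement*

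**What the plan says.** The supplement holds two linked protocols: the main PCV13 study (PCV13-HIV2011) and the PPV23 sub-study (PNEUMO-HIV 2011). The conflict lies in the sub-study.

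**HIV-positive group**
- Purpose statement at the end of the Rationale, second paragraph: the sub-study monitors "HIV-positive adults with previous PPV23 vaccination and in HIV-negative subjects, regardless their vaccination status".
- Study Design: the HIV-infected outpatients are "previously vaccinated , and unvaccinated HIV-negative subjects as a control" (the first two words describe the HIV-infected group, the rest the controls).
- Inclusion Criteria: "HIV with previous PPV23 vaccinatio (≤5years"), and as a separate bullet "HIV with CD4 ≥200 cells/µl in the last two evaluations before T0".
- Exclusion Criteria: "previous PPV23 or PCV7 vaccination", not restricted to either group and without a time limit.
- Sample size and study group selection: by application of these criteria, "50 HIV-infected adult outpatients and 100 subjects HIV negative will be prospectively enrolled". The HIV-positive subjects then receive one PPV23 dose at baseline.

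**HIV-negative group**
- Inclusion Criteria: "HIV negative regardless vaccination status". The second paragraph of the purpose statement agrees.
- The first paragraph of the purpose statement and the Study Design call these subjects unvaccinated.
- The exclusion line, unrestricted, also applies to them.

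**Main study, for comparison**
- Its exclusion list is identical. There it fits, because its Study Design recruits patients "aged 18–65 years with CD4 counts ≥200 cells/µL, pneumococcal vaccine-naïve".

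**The concern.** Centres screen against the eligibility lists. Here the two lists give opposite instructions on vaccination history, so a centre can enrol the described HIV-positive group only by disregarding one of them. Nothing says which, and two centres could decide differently.

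The choice determines what is measured:
- The third and fourth primary outcomes (serological response to one PPV23 dose; its effect on carriage and invasive disease) concern a first dose in patients without earlier PPV23 and a revaccination in patients with it. The sub-study's own Rationale says that repeated polysaccharide exposure can blunt the response, so the two are not interchangeable.
- In the HIV-positive part of the first and second primary outcomes, baseline antibody is either left over from a vaccine or naturally acquired.
- The planned comparison with the main study sets vaccine-naive patients against either previously vaccinated or other naive patients.

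If the exclusion line is followed, the two studies also compete for the same patients: the centres and calendar dates are identical, and no rule assigns a patient to one study or the other.

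**Working it through.** The plan gives 50 and 100 as planned numbers without a calculation, so there is no figure to reproduce. The check is one of logic: list the possible subject profiles and apply both lists to each.

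**Inputs**
- Prior vaccine: none; PPV23 within 5 years; PPV23 more than 5 years ago; PCV7.
- CD4 at least 200 in the last two evaluations: yes or no (HIV-positive only).
- Excluded if prior vaccine is PPV23 or PCV7 (Exclusion Criteria).
- Eligible = meets inclusion AND NOT excluded.

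The status bullets of the Inclusion Criteria cannot all apply to one person, since one of them is for HIV-negative subjects. Two readings are therefore possible for HIV-positive subjects:
- *Joint*: PPV23 within 5 years AND CD4 at least 200.
- *Alternatives*: PPV23 within 5 years OR CD4 at least 200.

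**HIV-positive: 4 × 2 = 8 profiles**

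| Prior vaccine | CD4 ≥200 | Included (joint) | Included (alternatives) | Excluded | Eligible (joint) | Eligible (alternatives) |
|---|---|---|---|---|---|---|
| None | yes | no | yes | no | no | **yes** |
| None | no | no | no | no | no | no |
| PPV23 ≤5 y | yes | yes | yes | yes | no | no |
| PPV23 ≤5 y | no | no | yes | yes | no | no |
| PPV23 >5 y | yes | no | yes | yes | no | no |
| PPV23 >5 y | no | no | no | yes | no | no |
| PCV7 | yes | no | yes | yes | no | no |
| PCV7 | no | no | no | yes | no | no |

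- Joint: 0 of 8 profiles are eligible, so 0 of the 50 planned subjects. The single profile that meets inclusion is the one the exclusion removes.
- Alternatives: 1 of 8 is eligible, the unvaccinated patient with adequate CD4. This is the opposite of the population in the purpose statement and Study Design.
- Both readings: 0 of the 4 profiles with earlier PPV23 are eligible.

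**HIV-negative: 4 profiles.** All 4 meet inclusion and 3 are excluded, so 1 of 4 (no prior vaccine) is eligible, although the inclusion bullet admits any vaccination status.

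**Range in practice.** If centres disregard the exclusion line and require earlier PPV23, 50 of 50 are previously vaccinated. If they apply the exclusion line and disregard the PPV23 requirement, 0 of 50 are. If practice varies, any number between is possible. The documents give no basis for a point within 0 to 50.

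**The case against.** The strongest defence is that the intent is plain. The purpose statement, the Study Design and the Inclusion Criteria all point to previously vaccinated HIV-positive patients, and the exclusion list looks carried over from the main study. The sub-study's visit schedule likewise still refers to a second PCV13 dose, which the sub-study does not give. A sensible investigator would ignore the stray line.

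The point about intent stands: it would be wrong to say that the documents give no indication of whom they meant to enrol. It does not mend the operative criteria, which govern screening and which the enrolment section invokes. Nor does the rest of the text settle the matter. A baseline PPV23 dose is compatible with patients who never had it, and the first paragraph of the purpose statement could refer to an earlier dose or to the study dose.

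Four stronger conclusions are tempting and are not supported:
- *That no HIV-positive subject at all can enter.* This needs the joint reading. That reading is the more natural one, but the alternatives reading admits unvaccinated patients.
- *That all four primary outcomes fall.* The first two also cover the 100 HIV-negative subjects, whose contribution does not depend on the HIV-positive group.
- *That a mixed group could not be interpreted.* It could be analysed by documented vaccine history. The plan collects anamnestic data at baseline but does not name vaccine history among them.
- *That the exclusion line is simply wrong for HIV-negative subjects.* It conflicts with the inclusion bullet but agrees with the sections that call these subjects unvaccinated. The text is inconsistent about this group even without the exclusion line.

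**Conclusion.** Wrong as written. The sub-study's inclusion and exclusion lists contradict each other on vaccination history, and no other section resolves it. On any reading, no HIV-positive subject with previous PPV23 can enter. The joint reading leaves 0 of 50 eligible; the alternatives reading leaves only patients without PPV23 or PCV7. Between 0 and 50 of the 50 could be previously vaccinated in practice, and the meaning of the HIV-positive results in all four primary outcomes changes with that number.

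The HIV-negative group has a separate inconsistency: any vaccination status in two places, unvaccinated in two others, with an exclusion for PPV23 or PCV7 on top.

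The conclusion rests on reading the exclusion line as it stands, for all subjects and without a time limit. The main study's own criteria are consistent on this point; it is touched only through the planned comparison and, if a naive group is chosen, through competition for patients.

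**What to change.** Amend the sub-study so that its purpose statement, Primary Outcome Measures, Study Design, Inclusion Criteria, Exclusion Criteria and the section on sample size and group selection agree:

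1. State one vaccination-history criterion for the HIV-positive group and one for the HIV-negative group, with the same wording throughout.
2. Limit the exclusion line to the group it is meant for, and name every pneumococcal vaccine concerned. PCV13 appears in neither eligibility list.
3. If an HIV-positive group without earlier vaccination is chosen, add a rule that separates recruitment to the sub-study from recruitment to the main study.
4. State in the Primary Outcome Measures whether the PPV23 outcomes concern a first dose or a revaccination.
5. Record documented vaccine history (product and date) at baseline, and analyse anyone already enrolled by that history.

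Which population is studied is for the investigators to decide; the review asks only that the sections be reconciled. The cost is a short protocol amendment and a vaccine-history entry on the baseline form, with no additional patients or procedures.

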**Sample size and study group selection**

Applying these criteria, 50 HIV-infected adult outpatients who had never been vaccinated with any pneumococcal vaccine will be prospectively enrolled at two Infectious Diseases Clinical Centers in Central Italy (University Division of Infectious Diseases in Siena and Institute of Clinical Infectious Diseases, Catholic University of the Sacred Heart in Rome). All subjects will be required to sign a written informed consent before enrolling in the study.

At baseline (day 0, time of first vaccine dose administration), demographic, clinical and laboratory characteristics will be collected by patients interview.

At baseline, the enrolled patients will received two doses of the 13-valent vaccine (PCV13 Prevenar13®, Wyeth Vaccines) eight weeks apart.

Follow-up visits will be scheduled at 8 (time of second PCV13 dose), 24 and 48 weeks. At baseline and at each visit clinical and anamnestic data from patients will be recorded; peripheral venous blood samples will be collected to assess humoral immune response against PCV13 serotype; nasopharyngeal swabs will be collected, in order to investigate the *S. pneumonia* presence. CD4+ T cell count and plasma HIV-RNA will be also monitored.

After each vaccine administration, short- (30 minutes), medium- (≤5 days) and long-term adverse reactions will be monitored.

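### Sub-study PNEUMO-HIV 2011 both requires and excludes prior PPV23 in HIV-positive patients, so as written none is eligible; the vaccination rule for HIV-negative subjects is also inconsistent

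*Supplement*

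**What the plan says.** All of this concerns sub-study PNEUMO-HIV 2011 unless the main study (PCV13-HIV2011) is named.

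**HIV-positive patients**
- Inclusion Criteria: "HIV with previous PPV23 vaccinatio (≤5years", plus a CD4 condition.
- Purpose statement after the Rationale, second paragraph: the sub-study is "for a microbiological and serological monitoring in HIV-positive adults with previous PPV23 vaccination".
- Study Design: the HIV-infected outpatients are "previously vaccinated , and unvaccinated HIV-negative subjects as a control" (the first two words describe the HIV-infected group).
- Exclusion Criteria: "previous PPV23 or PCV7 vaccination", with no qualification.

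**HIV-negative subjects**
- Inclusion Criteria: "HIV negative regardless vaccination status". The second paragraph of the purpose statement agrees: "in HIV-negative subjects, regardless their vaccination status".
- First sentence of the purpose statement: "following vaccination with one dose of PPV23, and in unvaccinated HIV-negative subjects". Study Design also calls them unvaccinated.
- The exclusion bullet applies to them as to everyone else.

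**Enrolment and dosing.** Sample size and study group selection enrols 50 HIV-positive and 100 HIV-negative subjects by reference to these two lists. It gives the HIV-positive patients one PPV23 dose at baseline and the HIV-negative subjects no vaccine. It also labels week 8 as the visit for a second dose of PCV13, a vaccine the sub-study does not give.

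**Main study.** The same exclusion bullet appears there, and it fits: the population is "50 HIV-infected adult outpatients who had never been vaccinated with any pneumococcal vaccine".

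**The concern.** Sites screen against the inclusion and exclusion lists. Here one list makes prior PPV23 a condition of entry for HIV-positive patients and the other makes it a bar. Enrolling any HIV-positive patient therefore breaks one criterion or the other, and nothing in the protocol says which gives way. The HIV-positive patients are the sub-study's only vaccinated and followed-up group, and the third and fourth primary outcomes (serological response to PPV23, and its effect on carriage and invasive disease) rest entirely on them.

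For HIV-negative subjects, the rule decides whether baseline titres may include vaccine-induced antibody. Those titres enter the first two primary outcomes: colonization in relation to baseline titre, and baseline serology in both groups.

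A conditional point follows. If previously vaccinated patients do receive PPV23 at baseline, as the dosing sentence says, the third and fourth primary outcomes concern a repeat dose within 5 years of an earlier one. The sub-study's own Rationale warns that repeated polysaccharide exposure can blunt the response, so first dose and repeat dose are different questions.

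**Working it through.** The documents give no derivation for the 50 and 100, so there is no sample-size figure to reproduce. The check is one of logic, with eligible = meets inclusion AND NOT meets exclusion.

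**1. HIV-positive group**
- Required (Inclusion Criteria): PPV23 within the last 5 years.
- Barred (Exclusion Criteria): any earlier PPV23 or PCV7.
- Everyone in the required set is in the barred set, so the remainder is empty: 0 of 50.

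**2. Can another reading rescue it?** The two HIV bullets in the Inclusion Criteria could be taken as alternatives, so that a vaccine-naive patient with adequate CD4 enters through the CD4 bullet. The PPV23 bullet would then still admit nobody. The reading also conflicts with the second paragraph of the purpose statement and with Study Design, both of which describe this group as already vaccinated. No amendment or other text limits the exclusion.

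**3. Where the bullet probably came from**

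| List | Main study | Sub-study | Comparison |
|---|---|---|---|
| Exclusion bullets | 7 | 7 | 7 of 7 identical |
| Inclusion bullets | 4 | 6 | 3 unchanged, 1 reworded (CD4), 2 new (both on vaccination history) |

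The inclusion list was adapted to the new population and the exclusion list was not. Carry-over is an inference, but the stray PCV13 label at week 8 points the same way.

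**4. HIV-negative group**
- Inclusion Criteria and second paragraph of the purpose statement: any vaccination history.
- Exclusion Criteria: no prior PPV23 or PCV7.
- First sentence of the purpose statement and Study Design: unvaccinated. This may mean only that they receive no vaccine on study, which Sample size and study group selection confirms.

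A never-vaccinated control satisfies every one of these statements, so the group is narrowed and not emptied. The number affected is 100 × p, where p is the proportion with prior PPV23 or PCV7. The documents do not give p. Purely as assumptions:

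| p | Affected, of 100 |
|---|---|
| 0% | 0 |
| 5% | 5 |
| 10% | 10 |
| 20% | 20 |

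The logical bounds are 0 and 100.

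**5. Which PPV23 dose is studied?** The dosing sentence gives PPV23 at baseline to patients who, by the Inclusion Criteria, had it within 5 years: a repeat dose. The purpose statement's language of monitoring would also fit a study in which the single dose is the earlier one, but that does not fit the dosing sentence. The dosing paragraph also carries main-study text, so it is not certain evidence either.

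**The case against.** The strongest reply is that the intended population can be recovered. Three places (Inclusion Criteria, purpose statement, Study Design) describe previously vaccinated HIV-positive patients, one of them with a specific 5-year window. Against them stands a single generic bullet that looks copied. Most readers would let the specific criterion prevail, and the practical harm would be protocol deviations and unclear screening that one amended line cures. Nothing in the documents shows that an estimate or a test would change.

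Much of that is fair. It supports the proposed correction and means that 0 of 50 should not be read as a recruitment forecast. It does not remove the fault: an eligibility list is applied as written, and this one gives a wrong result when followed.

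Other limits also stand:
- If unvaccinated means only not vaccinated on study, the HIV-negative inconsistency reduces to the same stray bullet. The assumed percentages say nothing about its real size.
- The repeat-dose question comes from the Inclusion Criteria and the dosing sentence, and would exist without the exclusion bullet.
- The difference in vaccination history from the main study's vaccine-naive patients is a feature of the design and would remain after the correction.
- The week-8 label has no bearing on eligibility.

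None of these secondary points is needed for the main conclusion.

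**Conclusion.** The concern holds, with high confidence, and must be fixed. It rests on the inclusion and exclusion bullets for HIV-positive patients and on the enrolment statement that applies both lists; no numerical assumption is involved. The HIV-negative inconsistency is real but smaller, and its size cannot be determined from the documents. Whether the third and fourth primary outcomes concern a repeat dose depends on the sponsor confirming the baseline PPV23 dose. The fault is confined to the sub-study.

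**What to change.** 1. **Exclusion Criteria, HIV-positive patients:** remove prior PPV23. The PCV7 exclusion can stay for them.
2. **HIV-negative subjects:** choose one rule and make the purpose statement, Study Design, Inclusion Criteria and Exclusion Criteria agree with it. Either any vaccination history is allowed, in which case the exclusion does not apply to them and unvaccinated becomes not vaccinated on study; or they must never have been vaccinated, in which case the wording that admits any history is deleted.
3. **Sample size and study group selection:** delete the PCV13 label at week 8.
4. **Baseline PPV23 dose:** confirm whether it is intended.
   - If it is, describe the third and fourth primary outcomes as the response to, and effect of, a repeat PPV23 dose within 5 years of an earlier one.
   - If it is not, and the sub-study only monitors patients after their earlier dose, correct the dosing sentence and reword those two outcomes to match.
5. **Comparison with the main study** (purpose statement and Statistic Analysis): if the baseline dose is confirmed, state that any comparison with the vaccine-naive PCV13 patients is confounded by vaccination history.

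The cost is an amendment to wording in the sections named, and in Primary Outcome Measures depending on item 4. No extra patients or visits are needed.

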**Sample size and study group selection**

Applying these criteria, 50 HIV-infected adult outpatients and 100 subjects HIV negative will be prospectively enrolled at two Infectious Diseases Clinical Centers in Central Italy (University Division of Infectious Diseases in Siena and Institute of Clinical Infectious Diseases, Catholic University of the Sacred Heart in Rome). All subjects will be required to sign a written informed consent before enrolling in the study.

At baseline, demographic, clinical and laboratory characteristics will be collected by patients interview.

At baseline, the enrolled HIV-positive patients will received one dose of the 23-valent vaccine (PPV 23); follow-up visits will be scheduled at 8 (time of second PCV13 dose), 24 and 48 weeks.

At baseline and at each visit clinical and anamnestic data from patients will be recorded; peripheral venous blood samples will be collected to assess humoral immune response against PPV23 serotype; nasopharyngeal swabs will be collected, in order to investigate the *S. pneumonia* presence. CD4+ T cell count and plasma HIV-RNA will be also monitored.

After each vaccine administration, short- (30 minutes), medium- (≤5 days) and long-term adverse reactions will be monitored.

Oppositely, HIV negative subjects will not receive any vaccination; only at baseline clinical and anamnestic data will be recorded; peripheral venous blood samples will be collected to assess humoral immune response against PPV23 serotype; nasopharyngeal swabs will be collected, in order to investigate the *S. pneumonia* presence.

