**Primary Outcome Measures:**

- Determine the rate of nasal colonization by different pneumococcal serotypes in HIV-positive and HIV-negative adults, in relation to baseline antibody titers at T0;
- Determine the basal serological response (qualitative and quantitative) in HIV-positive and HIV-negative adults;
- Define serological response after one dose of PPV23 vaccine in HIV+ adults;
- Evaluate the effect of one dose of PPV23 vaccine in terms of nasal pneumococcal carriage and occurrence of invasive pneumococcal diseases;

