**Study duration: 24 months**

**Phase I:** 12 months(November, 1st 2011 – November, 1st 2012) enrolling + microbiological and serological screening.

**Phase I:** 12 months(November, 1st 2012 – October , 31st 2013) serological and microbliological analyses and data elaboration.

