**Clinical follow-up**

Subjects will be considered colonized by S. pneumoniae with at least one positive nasopharingeal swab. Colonized patients will be followed for the next 12 months so to observe potential invasive infections. Potential simultaneous colonization by two or more serotypes will be highlighted through the analysis of isolated colonies.

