**STATISTIC ANALYSIS**

Clinical and anamnestic data collected at enrolment and at each follow-up visit, will be integrated with microbiological and serological results and correlation analyses will be performed. Further statistical analyses will be carried out considering the results from this study and from the main study (protocol code PCV13-HIV2011).

To evaluate the immunological response, the geometric mean concentrations of IgG (GMCs) at baseline, 4,8,24 e 48 week will be calculated. The GMCs will be compared by Student's' t Test (For Paired Samples). The quantitative variable will be tested for normal distribution and compared by

Mann-Whitney or Kruskal-Wallis test.

Differences in proportion will be determined by chi squared test or fischer exact test.

Regression or logistic analyses (univariate and multivariate) will asses the association with colonization, infection, antibiotic resistance, and an efficient immune response (e.g. ≥0.35μg/mL).

Analyses were performed using the SPSS software package (version 17.0 Chicago, IL).

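### Nothing balances HIV-positive patients and HIV-negative controls by calendar time or centre, so the sub-study's first carriage comparison is open to confounding

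*Supplement*

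**What the plan says.** All references are to the sub-study protocol (PNEUMO-HIV 2011) in the Supplement.

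- Primary Outcome Measures, first item: "Determine the rate of nasal colonization by different pneumococcal serotypes in HIV-positive and HIV-negative adults, in relation to baseline antibody titers at T0". The fourth item is the effect of one dose of PPV23 on carriage and invasive disease.
- Study Design gives the comparison group its role: "unvaccinated HIV-negative subjects as a control".
- Sample size and study group selection: "50 HIV-infected adult outpatients and 100 subjects HIV negative will be prospectively enrolled at two Infectious Diseases Clinical Centers in Central Italy". HIV-positive patients are swabbed and bled at baseline and again later: "follow-up visits will be scheduled at 8 (time of second PCV13 dose), 24 and 48 weeks". Controls are seen once: "HIV negative subjects will not receive any vaccination; only at baseline clinical and anamnestic data will be recorded".
- Study duration gives one window for everyone: "12 months(November, 1st 2011 – November, 1st 2012) enrolling + microbiological and serological screening".
- Clinical follow-up defines a carrier: "Subjects will be considered colonized by S. pneumoniae with at least one positive nasopharingeal swab".
- Statistic Analysis: "Differences in proportion will be determined by chi squared test or fischer exact test". The same section plans univariate and multivariate regression or logistic analyses of association with colonization, without naming a covariate.

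No section matches, paces or stratifies the two groups by date or centre.

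**The concern.** The HIV-positive against HIV-negative contrast is observational, so it is only as good as the comparability of the two groups. A centre could recruit its controls in a few convenient weeks while patients accrue through the year, or one centre could supply most of the controls, and both would comply with the plan. If carriage also varies by season or between the two cities, the observed difference mixes HIV status with time and place. It could show a gap where HIV has no effect, or mask a real one. This is a primary outcome, and a recruitment pattern cannot be repaired afterwards: if the groups barely overlap in time or place, regression has no data from which to separate HIV from season or centre.

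**Working it through.** **Inputs from the documents.** 50 HIV-positive and 100 HIV-negative subjects; one baseline visit for controls; baseline plus weeks 8, 24 and 48 for patients; chi-squared or Fisher test. The plan states no power, significance level or carriage rate for this contrast, so there is no figure of its own to reproduce.

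**Assumptions.** Two strata (season or centre) with carriage *high* and *low*, a two-sided 5% level, and the uncorrected chi-squared test with its rejection probability enumerated exactly for 50 against 100.

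**Step 1: a spurious gap with no HIV effect.** Group carriage is p = w × high + (1 − w) × low, where w is the share of the group in the high stratum. The gap is therefore (w₁ − w₂) × (high − low). For 15% and 5% with w = 0.6 and 0.4: 0.6 × 15 + 0.4 × 5 = 11% against 0.4 × 15 + 0.6 × 5 = 9%, a gap of 2 points. Each cell gives the gap in points and the rejection rate:

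| Mix in the two groups | 10% v 5% | 15% v 5% | 20% v 5% |
|---|---|---|---|
| 50/50 v 50/50 | 0; 4.5% | 0; 4.9% | 0; 5.1% |
| 60/40 v 40/60 | 1; 5.6% | 2; 7.5% | 3; 9.4% |
| 70/30 v 30/70 | 2; 7.8% | 4; 13.9% | 6; 20.9% |
| 90/10 v 10/90 | 4; 15.9% | 8; 38.2% | 12; 61.6% |
| Complete separation | 5; 21.9% | 10; 54.5% | 15; 81.0% |

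**Step 2: a real difference hidden.** Let HIV double carriage within each stratum, with 15% and 5% in controls. A balanced mix shows 20% against 10% (10 points, power 40.8%). If 40% of patients and 60% of controls fall in the high stratum, it shows 18% against 11% (7 points, 23.8%). With 30% and 70% it shows 16% against 12% (4 points, 11.7%). With 10% and 90% the sign reverses: 12% against 14%.

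**Step 3: unequal numbers of swabs.** The carrier definition counts any positive swab and is not limited to T0. Patients have up to four swabs and controls have one. With equal per-swab carriage of 10%, four independent swabs give 1 − 0.9⁴ = 34.4% against 10%. If persistent carriage makes the four worth two independent swabs, the result is 1 − 0.9² = 19.0% against 10%. Matching on month and centre would not remove this.

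**Step 4: change after PPV23.** Week 24 is 168 days after T0. Week 48 is 336 days, 29 short of 365. Assume two seasons of 182.5 days at 15% and 5%. If enrolment is even over the year, every visit has half its swabs in each season and season cancels in the group mean. If all patients enrol evenly within the high season, 168/182.5 = 92% of week-24 swabs fall in the low season, a spurious fall of 0.92 × 10 = 9.2 points. At week 48 the figures are 29/182.5 = 16% and 1.6 points.

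**Step 5: room for adjustment.** At 5% to 15% carriage, 150 subjects yield 7.5 to 22.5 carriers. A model with HIV status, centre and binary season then has 2.5 to 7.5 carriers per term.

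**The case against.** The strongest reply is that both groups are enrolled at the same two centres in the same 12-month window, so they may well end up balanced. Nothing in the documents shows that they will differ in month or centre, or that carriage varies by either. One culture and identification procedure is laid down for all swabs. The planned multivariate regression could include centre and month: adjustment is neither promised nor excluded. At 60/40 the bias is 1 to 3 points across the table, in a pilot that (normal approximation, assumed 5% level) has 80% power at 10% control carriage only for 28.5% in patients. All of this stands, and it limits the size of the point. It does not supply a safeguard.

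Three stronger readings are tempting, and the documents do not support them.

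- A reader might infer that sampling controls once itself produces season or centre bias. It does not: a T0-to-T0 comparison uses one swab per person in both groups, and bias needs imbalance as well as variation in carriage.
- A reader might take the complete-separation figures as the expected error. They are the extreme case.
- A reader might infer that any change from T0 to week 24 measures season. That is so for an individual, but for the group only if enrolment clusters in part of the year.

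The argument also concerns carriage more than IgG, since all sera are tested in one laboratory.

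**Conclusion.** The point holds as an unguarded route to confounding in a primary comparison; it does not demonstrate a bias. The plan neither balances the groups by calendar time and centre nor commits to adjusting for them. The size depends wholly on assumed rates and mixes. With strata at 15% and 5%, mild imbalance costs about 2 points and moderate imbalance 4, while strong imbalance gives 8 to 10 points and can reverse a true difference. The any-positive-swab definition is a firmer, separate threat to the same contrast if it is applied to all visits: the outcome ties the antibody titres to T0 but does not say that the swab is the T0 one.

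**What to change.** 1. For each HIV-positive sub-study patient, enrol two HIV-negative subjects at the same centre and in the same month or calendar quarter. The planned 1:2 ratio already allows this.
2. State that the HIV-positive against HIV-negative carriage comparison uses the T0 swab only.
3. Name centre and a binary season term in that comparison, or stratify by them, and add further terms sparingly because few carriers are expected.
4. For change in carriage after PPV23, tabulate swabs by season at each visit and give T0 against week 48 as the near season-matched contrast. Report week 24 with its season mix shown, since season affects it only if enrolment clusters.

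No patients, samples or visits are added, and centre and date are already in the visit records. The costs are that control recruitment is paced by patient recruitment, and that adjustment loses some precision with few events.
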